## Abstract

**Background:**

Chronic subdural hematoma (CSDH) is a common disease that is more prevalent in older people. Surgical intervention is a safe treatment of choice. However, the recurrence rate is relatively high and the outcome is not always satisfactory among surgically treated patients. It is believed that aberrant angiogenesis and intracapsular inflammation contribute to the development of CSDH. Atorvastatin is reported to promote angiogenesis and suppress inflammation. We have recently shown that atorvastatin is effective to non-surgically reduce and eliminate CSDH with minimal side effects. Here, we report a clinical research trial protocol that is designed to evaluate the therapeutic effects of atorvastatin on CSDH.

**Methods/Design:**

We have designed a multi-center, randomized, placebo-controlled, double blind clinical trial for evaluating the efficacy of oral atorvastatin in reducing CSDH. We have so far recruited 96 patients with CT-confirmed or MRI-confirmed CSDHs from 16 medical centers in China. These patients were originally recruited for the Oriental Neurosurgical Evidence-based Study Team (ONET) study. After informed consent is provided, patients are randomized to receive either atorvastatin (oral 20 mg/night for 8 weeks) or placebo (dextrin for 8 weeks); and followed for 16 weeks after the treatment. The primary outcome is the change in hematoma volume at the end of 8-week treatment. Secondary outcomes include: changes in 1) the hematoma volume at the 4^th^, 12^th^, and 24^th^ weeks; 2) Markwalder’s Grading Scale and Glasgow Coma Scale (MGS-GCS); 3) Glasgow Outcome Score (GOS) and 4) Activities of Daily Life – the Barthel Index scale (ADL-BI). Safety will be assessed during the study by monitoring adverse events, laboratory tests, electrocardiography (ECG), measurements of vital signs (temperature, pulse, and blood pressure) and body weight.

**Discussion:**

Results of this trial will provide critical information regarding whether atorvastatin is an effective and safe alternative to surgical treatment of CSDH.

**Trial registration:**

ClinicalTrials.gov Identifier – NCT02024373

The date of trial registration: 7 August 2013

**Electronic supplementary material:**

The online version of this article (doi:10.1186/s13063-015-1045-y) contains supplementary material, which is available to authorized users.

## Background

Chronic subdural hematoma (CSDH) is a common type of encephalic hematoma with an incidence of 5/10,000 in the general population and 58/10,000 in people who are 70 years or older [1]. Head trauma is the most common risk factor for CSDH [2], along with age. CSDH occurs in up to 26.5 % of patients who are 65 years or older. Older patients also have a significantly higher recurrence rate as compared to the general population [3]. Incidences of CSDH and recurrent CSDH are expected to raise worldwide with an aging population. In addition, the increasing use of anticoagulant/antiplatelet therapies is also a common risk factor for CSDH in patients without a history of trauma [4] and poses a challenge for the surgical treatment of CSDH. Unlike subacute subdural hematoma (SSDH), spontaneous reabsorption is rare in CSDH and surgery has traditionally been the treatment of choice [5]. However, the rate of recurrent CSDH is high (approximately 25 %) in surgically treated patients [6], leading to a mortality of 11.1–13.5 % [7]. The surgical outcome is particularly poor for patients of 90 years or older [8].

Because of unsatisfactory outcomes of surgery, several adjuvant or conservative therapies have been clinically tested, including corticosteroids, as complementary therapies [1]. Dexamethasone is reported to effectively reduce the volume of CSDH after surgery [9–12]. It is also reported that perindopril (angiotensin converting enzyme inhibitor, ACEI) reduces the recrudescence of CSDH after surgery [13]. We have recently reported the effect of atorvastatin on reducing CSDH in 23 patients [14].

The pathogenesis of CSDH and mechanisms of above adjuvant therapies remain poorly understood. It has been reported that a CSDH hematoma contains a large number of erythrocytes from continuous blood leakage due to primitively formed blood vessels in the hematoma wall. Vascular endothelial growth factor (VEGF) is detected at a significantly high level in hematoma and in the serum of CSDH patients. [15]. VEGF promotes angiogenesis, but, at a persistent high level, also inhibits the maturation of new vessels [16]. We have previously demonstrated the presence of a pseudo envelope around a subdural hematoma that contains immature and abnormal vessels [17]. In addition, a hematoma is also enriched in proinflammatory cytokines [18–20]. We and other have shown that statins (hydroxy-methylglutaryl-CoA reductase inhibitors) mobilize circulating endothelial progenitor cells (EPCs) to enhance angiogenesis [21–25]. Atorvastatin also inhibits VEGF and reduces the inflammatory reaction [26, 27] as well as up-regulating Notch1/Jagged1 signal, which is critical for VEGF-induced vessel formation and maturation. These reports led us to hypothesize that atorvastatin modulates VEGF expression and the level of inflammation in hematoma, resulting in the shrinkage of CSDH. This protocol was designed to test this hypothesis.

## Methods/Design

### Study objective

The primary objective of this trial is to evaluate the efficacy of atorvastatin in reducing or eliminating CSDHs after 2 months without surgery.

The secondary objectives are to evaluate changes in hematoma volume (non-enhanced computerized tomography (CT) scan) at the 4^th^ week during the treatment; and at the 12^th^ and 24^th^ weeks during the follow-up period; and to measure the effect of atorvastatin on improving neurological function in patients with CSDH as assayed by the MGS-GCS, GOS, and ADL-BI at 4 weeks, 8 weeks and 6 months after atorvastatin therapy is initiated.

### Trial design

The trial is designed as a multi-center, phase II, prospective, double blind, randomized, placebo-controlled study. Eligible patients are randomized in a 1:1 allocation ratio to one of the two treatment arms: 20 mg daily of atorvastatin (treatment) and placebo drug (control). The treatment will continue for 8 weeks followed by 16 weeks of follow-up.

Patients will be recruited from 16 neurosurgery centers in China that are participants in the Oriental Neurosurgical Evidence-based Study Team (ONET) (Table 1, additional ethics documentations in Additional file 1). ONET is chaired by the Department of Neurosurgery, Tianjin Medical University General Hospital. Before the enrollment, patients or their family guardians will be fully informed about the trial, its potential outcomes and adverse events; and provide informed consent. The informed consent forms are in Chinese and English. The study will be conducted according to the Declaration of Helsinki. The ethics boards of Tianjin Medical University General Hospital and other participating hospitals have approved this study.

**Table 1 Tab1:** Medical centers in China participating in the study

Medical centers	Ethics committee
1. Tianjin Medical University, General Hospital	Medical Ethics Committee of Tianjin Medical University General Hospital
2. Peking Union Medical College Hospital	Ethics Committee of Peking Union Medical College Hospital Affiliated to Chinese Academy of Medical Sciences
3. Prince of Wales Hospital, Hong Kong	Pharmacy and Poisons Board of Hong Kong
4. Qilu Hospital of Shandong University	Medical Ethics Committee of Qilu Hospital Affiliated to Shandong University
5. The First Affiliated Hospital of Zhengzhou University	Clinical Trial Ethics Committee of First Affiliated Hospital of Zhengzhou University
6. The Second Affiliated Hospital of Zhejiang University School of Medicine	Human Research Ethics Committee of the Second Affiliated Hospital of Zhejiang University School of Medicine
7. First Affiliated Hospital of Fujian Medical University	Medical Ethics Committee of First Affiliated Hospital of Fujian Medical University
8. First Affiliated Hospital of Shanxi Medical University	Science/Medical Experimental Ethics Committee of First Affiliated Hospital of Shanxi Medical University
9. General Hospital of Ningxia Medical University	Scientific Experiment Ethics Committee of Ningxia Medical University General hospital

### Inclusion criteria

The inclusion criteria are CSDH patients who: (1) are ≥ 18 and < 90 years old of either gender; (2) have evidence of supratentorial, unilateral or bilateral CSDH by CT scan (magnetic resonance imaging (MRI) scan is warranted if diagnosis is difficult); (3) have MGS-GCS < Grade 3 (Additional file 2); (4) have no cerebral herniation and immediate needs for surgery (as determined by 2 attending physicians); (5) have had no previous surgery on CSDH; and (6) fully understand the nature of this trial and provide informed consent.

### Exclusion criteria

The exclusion criteria are: (1) allergic to statins or their ingredients; (2) cerebral herniation; (3) subdural hematoma caused by tumors, hematologic diseases or other known severe comorbidities such as multiple organ failure, uncontrolled diabetes mellitus and heart failure; (4) abnormal liver function or liver diseases including uncontrolled hepatitis; (5) other diseases that may interfere with the study as determined by 2 attending neurosurgeons; (6) patients on oral statin medication for more than 1 week before randomization or who are expected to take statins in the next 6 months; (7) patients on oral steroids for more than 1 week before randomization or who are expected to take such medications in the next 6 months; (8) a participant in clinical trials in the past 4 weeks; (9) pregnancy or breastfeeding; (10) failure to complete the trial by poor compliance; (11) other conditions that render a patient unsuitable for the trial as determined by the study investigators.

### Medication and placebo

The 10-mg tablet of atorvastatin is provided by Pfizer, Inc. and taken orally at 20 mg daily before bed. The placebo drug matching oral atorvastatin is made of dextrin with the same weight and appearance and made by Shandong ARURA Pharmaceutical Research & Development. Co., Ltd. with the certification of good manufacturing practice (GMP) for pharmaceutical products issued by the China Food and Drug Administration (CFDA).

Atorvastatin and placebo are packed identically and labeled with packaging number, verification code, dosage, specifications, storage, batch number, the duration of usage, and manufacturer. The package will be labeled: “for clinical study use only.”

### Randomization

Eligible subjects are assigned randomly to either statin or placebo group through the Central Randomization System. The Data Acquisition System for Electronic Data Capture (DAS for EDC) 5.0 (Beijing Stemexcel Technology Co., Ltd., Beijing, China) will be used to produce random numbers. An EDC system is a computerized system designed for the collection of clinical data in electronic format for use mainly in human clinical trials. The ratio of experimental and control group is calculated, by a biostatistician independent of the study data management and statistical analysis, to be 1:1.

After initial screening, an investigator will log onto the Central Randomization System to enter demographic information of an enrolled patient to produce a random number application. A designated individual will then apply for a drug package number and dispense the drug when the package number is consistent with the one recorded in the database.

### Treatment and intervention

*Atorvastatin:* oral intake of a 20 mg Atorvastatin tablet daily for 8 weeks.

*Placebo:* oral intake of a placebo tablet daily for 8 weeks.

At the end of the 8-week treatment, the volume of hematoma will be evaluated by CT scan for the following outcomes:A hematoma disappears or is significantly reduced from the size measured before the treatment. Regardless of whether a smaller hematoma remains, the patient will enter into the follow-up period and should not be continuously treated with atorvastatin.A hematoma does not change significantly or increases by CT scan at the end of 8 weeks of treatment (this can occur in patients who receive placebo). At the end of atorvastatin treatment, attending surgeons can decide if these patients need to receive surgery. The detailed medication and treatment during the process will be continuously recorded for 24 weeks.For any patients whose hematoma increases as determined by CT scan and/or neurological deficits progress during the follow-up period, he or she may undergo surgery. The detailed medication and treatments during the process will be recorded for 24 weeks.

### Timeline schedule

Protocol-mandated assessments will be performed according to the schedule (Table 2). The study flow chart illustrates key steps of the trial (Fig. 1).

**Table 2 Tab2:** Visit and assessment schedule

Activities	Screening	Day 1	Days 2–6	Day 7	Week 2 ± 1D	Week 3 ± 1D	Week 4 ± 1D	Week 8 ± 3D (treatment end)	Week 12 ± 3D^4^	Week 24 ± 7D^4^
Informed consent	√									
History collection										
Inclusion/Exclusion	√									
Concomitant medication^1^		√	√	√	√	√	√	√	√	√
Physical examination	√			√	√	√	√	√	√	√
Surgery conversion		√	√	√	√	√	√	√	√	√
Efficiency observation										
Neurological symptoms^2^	√	√	√	√	√	√	√	√	√	√
Hematoma volume by CT^2^	√						√	√	√	√
MGS-GCS/ADL-BI^2^	√			√			√	√	√	√
GOS							√	√	√	√
Safety assessment										
Vital signs	√	√	√	√	√	√	√	√	√	√
Blood routine/Coagulation	√						√	√	√	√
Liver and renal function/Electrolyte/Lipids	√						√	√	√	√
Urinalysis	√							√		√
Electrocardiography	√							√		√
Pregnancy test	√									
Adverse events		√	√	√	√	√	√	√	√	√
Others										
Drug dispensing	√			√	√	√	√			
Drug recovery^3^				√	√	√	√	√		

*ADL-BI* Activities of Daily Life – the Barthel Index scale, *CT* computerized tomography, *D* day, *GOS* Glasgow Outcome Score, *MGS-GCS* Markwalder’s Grading Scale and Glasgow Coma Scale

^1^Records of combination therapy are required until the end of the trial

^2^Surgical therapy is considered in the case of deterioration in neurological symptoms and/or signs, MGS-GCS grading and increase of hematoma immediately imaging review then

^3^The remaining drugs need to be recovered

^4^At weeks 12 and 24, CT should be performed; other laboratory examinations will be selected when needed

**Fig. 1 Fig1:**
[figure not shown]
Flow chart to illustrate the design of the trial. *ADL-BI*, Activities of Daily Life – the Barthel Index scale, *AEs* adverse events, *ECG* electrocardiography, *GOS* Glasgow Outcome Score, *IWRS* Interactive Web Response System, *MGS-GCS* Markwalder’s Grading Scale and Glasgow Coma Scale

### Concomitant care

All patients in the study will receive routine laboratory assessments, including complete blood count (CBC), coagulation (international normalized ratio, INR), liver and renal function, blood lipids and urinalysis. Head CT images will be recorded in Digital Imaging and Communication in Medicine (DICOM) format and evaluated centrally in a triple-blinded manner. Blood samples will be analyzed in a local laboratory and saved in a Case Report Form (CRF) format. The 4 regular follow-up visits are scheduled at the 4^th^, 8^th^, 12^th^ and 24^th^ weeks after the initiation of atorvastatin treatment.

The ACEIs (such as perindopril, captopril, enalapril) are reported to eliminate CSDH [9, 28] and are thus their use is not allowed during the course of atorvastatin treatment. Anticoagulants (warfarin or new oral anticoagulants), antiplatelet drugs (aspirin, clopidogrel) or *Xuesaitong* (traditional Chinese medicine for activating blood circulation) can potentially interfere with hematoma absorption and are not recommended during the treatment. However, these patients will not be exclusively excluded from the trial participation. The following drugs may potentially interact with statins and/or cause adverse events [29] and will not be recommended during the treatment: red yeast rice, erythromycin, fibrates, cyclosporin, macrolide antibacterials, azole antifungals, tacrolimus, gemfibrozil, troglitazone, and itraconazole. The use of any medications will be recorded if they are used concomitantly during atorvastatin treatment in CRF, including name, dosing and duration of these medications.

Most participants are treated as outpatients receiving conventional and standard cares such as rest and pain relief. Family members are responsible for monitoring patients for progress in neurological symptoms such as worsening headache. If a patient is reported to have worsening symptoms, he or she will be further evaluated by two attending physicians for neurological deficits. These patients may be admitted during the trial for treatment of progressing neurological deficits and discharged when their symptoms are relieved significantly. Whether these patients remain on the trial as inpatients will be determined on a case-by-case basis by two participating investigators/surgeons.

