### SAEs

Severe adverse drug reaction/events (SAEs) refer to the following conditions: death, life-threatening or permanent or significant disability, permanent functional injury to the organs, hospitalization for emergencies or prolonged hospitalization.

Once a SAE is confirmed in a patient, this patient will be removed from the trial and a report should be filled within 24 hours. A full report regarding SAEs should be filled to the sponsor and SFDA. The ethics committee of pharmaceutical affairs of ONET will conduct an investigation to identify causes of SAEs and decide whether the trial will be terminated. The severity of SAE, its relationship with the trial medication, and treatments should be recorded in the CRF. The above conditions are delivered to the ethics committee of all participating hospitals.

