### Methodology

The ATOCH study is designed based on our previous experience in treating CSDH with atorvastatin, showing that 22 out of 23 patients achieved complete hematoma elimination during the follow-up period after atorvastatin treatment. We, therefore, expect a significant volume reduction in the hematomas of patients on atorvastatin. However, since this is a conservative treatment trial of a clinical condition that is traditionally treated surgically, we limit our recruitment to patients who have a small-medium volume of CSDH and whose MGS-GCS is less than 3. To reduce adverse risks, especially patients on placebo, all patients will be closely monitored for acute neurological deterioration. If neurological symptoms deteriorate during the trial, patients will receive an emergency head CT scanning and necessary surgery. Such patients will be removed from the trial.

Except for rhabdomyolysis and impact on liver function, atorvastatin is considered to be generally very safe. Thus, we do not plan to waive SAE for this trial protocol. If a patient develops any suspected related side effects, he or she will be immediately excluded. If atorvastatin-related side effects are confirmed, treatment will be terminated and affected patients will be followed for 6 months.

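### Patients who worsen before week 8 can be removed from the trial with no statement that their week-8 CT is still taken, and the discretionary stay rule conflicts with the SAE removal rule

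*Protocol article*

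**What the plan says.** Three sections of the protocol article decide whether a worsening patient stays in the trial.

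- **Concomitant care.** On admission: "These patients may be admitted during the trial for treatment of progressing neurological deficits and discharged when their symptoms are relieved significantly". On staying: "Whether these patients remain on the trial as inpatients will be determined on a case-by-case basis by two participating investigators/surgeons".
- **SAEs.** The definition includes "permanent functional injury to the organs, hospitalization for emergencies or prolonged hospitalization". The consequence is mandatory: "Once a SAE is confirmed in a patient, this patient will be removed from the trial".
- **Methodology.** On neurological deterioration, "patients will receive an emergency head CT scanning and necessary surgery. Such patients will be removed from the trial".

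Other text bears on what happens after removal.

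- Methodology says of suspected drug side effects: "If a patient develops any suspected related side effects, he or she will be immediately excluded". For confirmed ones, however, "treatment will be terminated and affected patients will be followed for 6 months".
- Treatment and intervention keeps a record to week 24 for patients whose surgery is decided at the end of treatment or who worsen during follow-up.
- Table 2 (Timeline schedule) has a surgery-conversion row from Day 1 to Week 24, and its second footnote says only that surgery is considered on deterioration.

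The primary outcome is the change in hematoma volume on CT at 8 weeks (Outcomes). The primary objective is "to evaluate the efficacy of atorvastatin in reducing or eliminating CSDHs after 2 months without surgery".

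**The concern.** A patient who worsens in, say, week 5 has probably had hematoma growth or persistence, so worsening is closely tied to the primary outcome. If that patient is removed and not scanned at week 8, the missing volume is not missing at random. If atorvastatin works, more such patients should come from the placebo arm, and the remaining placebo patients would look better than the arm as randomised. Blinding does not protect against this, because removal follows the clinical course and needs no knowledge of the allocation.

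There is also a conduct problem. Where one section gives discretion and another requires removal, two centres can treat similar patients differently while each follows the text. A scan that was never taken cannot be recovered by the analysis.

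Keeping operated patients does not settle everything. A week-8 CT after evacuation shows the effect of surgery, which the without-surgery objective cannot credit to either arm.

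**Working it through.** **Step 1: the rules side by side, for worsening before week 8**

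| Situation | Concomitant care | SAEs | Methodology |
|---|---|---|---|
| Admitted, neither emergency nor prolonged, no surgery | Two investigators decide | Not triggered by the admission | Not triggered on the narrow reading |
| Emergency or prolonged admission, no surgery | Two investigators decide | Removed once the SAE is confirmed | Not triggered on the narrow reading |
| Emergency CT and surgery | Two investigators decide, if admitted for progressing deficits | Removed if the admission is a confirmed SAE | Removed |

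The firm conflict is in the second row, between Concomitant care and SAEs. On the narrow reading, Methodology removes only patients who go on to emergency CT and surgery. It can then be read as a further step after Concomitant care.

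**Step 2: is follow-up after removal stated?**

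- Confirmed side effects: yes, 6 months (Methodology).
- Surgery decided at the end of week 8, or worsening in the follow-up period: medication and treatments are recorded for 24 weeks (Treatment and intervention).
- Worsening, surgery or an SAE unrelated to study drug before week 8: nothing is stated either way.

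The gap covers exactly the period that feeds the primary outcome.

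**Step 3: what loss of these volumes could do**

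The plan has no figure of its own to reproduce on this point. Everything below is illustration. It uses 100 patients per arm (Sample size) and a two-sided 5% test (Data analysis). The removal fractions are assumptions.

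*Responder version.* The Sample size section assumes 80% against 50% achieve reduction. Per 100, non-responders are 20 and 50. Suppose a fraction f of non-responders in each arm is removed. The observed rate is responders / (100 − removed).

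- f = 20% (4 against 10 removed): 80/96 = 83.3% and 50/90 = 55.6%. The difference is 27.8 points against a true 30.0; power 0.988.
- f = 40% (8 against 20 removed): 80/92 = 87.0% and 50/80 = 62.5%. The difference is 24.5 points; power 0.964.
- The odds ratio stays at 4.0 in both, because the same fraction of non-responders is removed from each arm.

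*Continuous version, closer to the stated primary outcome.* Assume a true difference of 0.5 SD (atorvastatin mean 0.5, placebo mean 0), removed patients at −1 SD in both arms, and an SD of 1 among those who remain. With removal fraction r, the retained mean is (arm mean + r) / (1 − r).

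- No removal: 0.50 SD; power 94%.
- 4% against 10%: 0.54/0.96 − 0.10/0.90 = 0.563 − 0.111 = 0.45 SD; power 87%.
- 8% against 20%: 0.58/0.92 − 0.20/0.80 = 0.630 − 0.250 = 0.38 SD. The standard error is √(1/92 + 1/80) = 0.153 and z = 2.49, so power is about 70%.
- 5% against 20%: 0.33 SD; power 58%.
- 10% against 30%: 0.24 SD; power 32%.

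*Direction.* Equal 5% removal of non-responders gives 80/95 − 50/95 = 84.2% − 52.6% = 31.6 points, above the true 30.0. The bias can therefore go either way.

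**Step 4: why operated patients need a handling rule even if scanned**

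Suppose all affected patients have surgery and the evacuated week-8 CT were counted as reduction. At f = 20% the rates are 84% against 60%, 24.0 points, power 0.971. At f = 40% they are 88% against 70%, 18.0 points, power 0.884. In this model that is worse than removal. Counting them as non-reduction leaves 30.0 points by construction.

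**The case against.** Several points can fairly be made for the plan.

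- **The conflict is narrow.** A reader might infer that all three sections contradict one another. The text does not support that. In Methodology the removal sentence follows directly on emergency CT and surgery, so its natural referent is the operated patient, and that rule and Concomitant care can be read as graded. What stands is the clash between Concomitant care and SAEs for emergency or prolonged admissions.
- **Removal is not defined as the end of follow-up.** A reader might infer that the plan discards these patients' week-8 scans. It does not say so. The surgery-conversion row in Table 2, the 6-month follow-up of confirmed side effects and the recording to week 24 all suggest continued tracking, and the full protocol may define the term. This stands in part: the harm is conditional. But none of those provisions expressly covers removal for worsening before week 8.
- **Analysis handling belongs in an analysis plan.** This stands. The document nowhere proposes to count an evacuated CT as reduction, so step 4 does not describe the plan; it shows only why a rule is needed. Which rule to use is a legitimate analysis-plan choice. Who stays under follow-up is a conduct rule, and the article states it.
- **Losses are already allowed for.** Sample size assumes 20% drop-out and then goes well beyond that, to 200 patients. This protects numbers, not against outcome-related loss.

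**Conclusion.** The point holds as a defect in stated conduct rules. Two of them cannot both be followed for an emergency or prolonged admission. For worsening before week 8, the removal wording leaves open whether the primary outcome is still measured.

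The bias is conditional on removal ending CT follow-up, and its size is unknown because the article gives no worsening, surgery or removal rate. The most likely direction is toward no effect, if placebo patients worsen more often, but the documents do not establish that. It would also be wrong to conclude from the responder illustration that power is safe. Power stays at 96% or more there only because equal fractions of non-responders are removed. Under the assumed continuous model, the same 8 against 20 removals take power from 94% to about 70%. Both figures rest on assumed fractions and effect sizes, and neither is an estimate for this trial.

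The sponsor should make the change because it is cheap and prevents an avoidable, outcome-related loss. The conflict in wording is certain; its effect on the result is not.

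**What to change.** Replace the case-by-case clause in Concomitant care and the removal wording in SAEs and Methodology with one rule:

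- Worsening, admission, surgery or an SAE may stop study drug. Every surviving randomised patient who has not withdrawn consent keeps the scheduled CTs to week 24, and all randomised patients stay in the analysis.
- Record the emergency pre-surgery CT and the date of surgery.
- Before unblinding, fix how patients operated on before week 8 are handled, so that a post-evacuation volume is not credited as drug or placebo reduction. Counting them as treatment failures is one option. Add a sensitivity analysis. The exact method can sit in the analysis plan.

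**Cost.** A wording amendment in a running trial (96 enrolled, Trial status) across 16 centres, with the ethics approvals of the participating hospitals, and a few extra visits and scans for patients who would otherwise have been removed. Volumes of patients already removed may not be recoverable. No interim analysis is planned, so the amendment disturbs no interim look.
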